### Interim analyses {21b}

Not applicable, as no interim analyses are planned in this study.

### Methods for additional analyses (e.g., subgroup analyses) {20b}

Not applicable as, no additional analyses are planned in this study.

### Methods in analysis to handle protocol non-adherence and any statistical methods to handle missing data {20c}

The primary analysis will be based on the intention-to-treat (ITT) principle, but we will include only the randomized participants who participate in data collection at both the baseline and the study endpoint, irrespective of their degree of adherence to experimental food consumption. In this study, we will exclude randomized participants who drop out of the study and do not provide endpoint data, as this study aims to examine the effect of the nutritional supplement on healthy adults, and we do not expect as great an effect as when medication is administered to a patient group. To follow the ITT principle as closely as possible, all the participants will be asked to participate at the endpoint as much as possible. A per-protocol analysis limited to participants with adherence ratios greater than 80% will be performed as a sensitivity analysis. Every effort will be made to prevent missing values during the data collection process, and we will address any missing data using multiple imputation or regression imputation.

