### Criteria for discontinuing or modifying allocated interventions {11b}

We do not expect serious adverse effects to occur after consumption of the brown rice-based supplement or the placebo. However, if a participant wishes to discontinue the consumption of experimental products due to poor physical condition experienced during the intervention period, the intervention will be stopped for that individual. In the event of an allergic reaction to the experimental products, the intervention will be stopped immediately for the affected individual. The decision to discontinue consumption will be left to the individual participants, and any participant who chooses to discontinue the intervention will be asked to explain the reason. In this study, no modifications will be made regarding the allocated interventions or the dose of the experimental products.

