### Sample size {14}

This is the first study to simultaneously examine the effects of a brown rice-derived supplement on physical, cognitive and mental health; therefore, determining a uniquely valid sample size is not possible. Instead, we determined the sample size for this study (i.e., 40 participants in each group) by referencing an RCT that examined the effect of processed brown rice products on health, including the gut microbiota [13]. We will recruit 96 participants to allow for a potential 20% dropout rate.

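### The primary analysis is labelled intention-to-treat but is a complete-case analysis, its reason for excluding dropouts is unsound, and no planned analysis tests the effect of dropout

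*Protocol article*

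**What the plan says.** All the key statements stand in one paragraph of the protocol article, section {20c}.

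- Principle and set: the primary analysis is to rest on the intention-to-treat principle, but "we will include only the randomized participants who participate in data collection at both the baseline and the study endpoint".
- Exclusion: "we will exclude randomized participants who drop out of the study and do not provide endpoint data".
- Reason: the product is a nutritional supplement given to healthy adults, and "we do not expect as great an effect as when medication is administered to a patient group".
- Non-adherence: participants with endpoint data are kept "irrespective of their degree of adherence to experimental food consumption".
- Mitigation: "To follow the ITT principle as closely as possible, all the participants will be asked to participate at the endpoint as much as possible".
- Sensitivity analysis: a per-protocol analysis of participants with adherence above 80%.
- Missing data: the closing sentence promises multiple or regression imputation for whatever is missing.

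Elsewhere, Sample size {14} says "We will recruit 96 participants to allow for a potential 20% dropout rate". Statistical methods {20a} frames the co-primary analyses as a superiority comparison adjusted for relevant covariates, without naming the baseline value of the outcome as one. Outcomes {12} sets two measurement times for everything except daily health. Section {20b} plans no additional analyses.

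**The concern.** An intention-to-treat analysis takes all randomised participants in their allocated arm. A rule that admits only those measured at both visits conditions the comparison on something that happens after randomisation. If leaving the trial relates to how participants are faring, and does so differently in the two arms, the completer contrast mixes a product effect with a selection effect.

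The reason offered does not help. The size of the expected effect says nothing about why endpoint data would be missing. It points the other way: the smaller the effect sought, the smaller the attrition bias needed to hide or imitate it.

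The paragraph is also unsettled within itself. If dropouts are excluded, imputation can reach only gaps among attendees. If imputation is meant to cover missing endpoints, the exclusion cannot stand. Two analysts could take different primary sets from the same text. Read literally, the rule would also remove a dropout's recorded weeks from the daily-health comparison, which does not depend on the endpoint visit.

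**Working it through.** **1. How many are excluded.** Inputs from Sample size {14}: 40 per group, so 80; 96 recruited; 20% allowance.

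- The plan's figure reproduces as 80 × (1 + 0.20) = 96.
- On that arithmetic the budgeted loss is 96 − 80 = 16, or 16/96 = 16.7%.
- If 20% of those randomised drop out, 0.20 × 96 = 19.2 are excluded and 76.8 remain (38.4 per arm).

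The exclusion therefore covers about 16 to 19 of 96.

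**2. Does any other section restore them?** No. Section {20a} defines no other set, {20b} adds no analysis, and the per-protocol set in {20c} is narrower than the primary one. No planned analysis includes the dropouts.

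**3. What bias could result.** The document gives neither a dropout split by arm nor a completer–dropout difference, so the following inputs are assumptions. Take no true effect, SD 1, 48 randomised per arm and a two-sided 5% normal test. If a share d of an arm drops out and dropouts average g SD below completers, the completer mean exceeds the arm's true mean by d × g. With subscripts A and P for supplement and placebo:

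- bias = d_A g_A − d_P g_P
- SE = √[1/(48(1 − d_A)) + 1/(48(1 − d_P))]
- type I error = 1 − Φ(1.96 − bias/SE) + Φ(−1.96 − bias/SE)

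| Dropout A / P | g in A / P | Bias (SD) | SE | Type I error |
|---|---|---|---|---|
| 20% / 20% | equal | 0 | 0.228 | 5.0% |
| 20% / 20% | 0.5 / 0 | 0.10 | 0.228 | 7.2% |
| 20% / 20% | 1.0 / 0 | 0.20 | 0.228 | 14.2% |
| 30% / 10% | 0.25 / 0.25 | 0.05 | 0.230 | 5.5% |
| 30% / 10% | 1.0 / 1.0 | 0.20 | 0.230 | 14.0% |

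For the second row: 0.20 × 0.5 − 0.20 × 0 = 0.10; SE = √(2/38.4) = 0.228; ratio 0.438; rejection rate 7.2%.

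**4. The role of the baseline covariate.** A simulation assumed 96 randomised, no true effect, nominal dropout of 25% versus 15%, supplement-arm dropout dependent on baseline status, and a baseline–endpoint correlation of 0.6.

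- Completers, endpoint only: bias about 0.15 SD, rejection about 9%.
- Completers, change score (similar scenarios): bias about 0.09 to 0.12 SD in the opposite direction, rejection about 7 to 8%.
- Completers, baseline value as covariate: bias about 0, rejection 4.4%.

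The result thus turns on whether the baseline value is in the model, which {20a} does not say. No such adjustment removes bias from dropout that depends on unobserved outcomes.

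**The case against.** The strongest reply is that the departure is open. The sentence that names ITT also states the restriction, and the paragraph claims only to follow the principle as closely as it can. Non-adherers who attend the endpoint stay in, all participants are asked to attend, and section {18b} adds incentives for complete endpoint data. This stands: the fault is a wrong label and a wrong reason, not concealment, and the set is not a per-protocol set.

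Three stronger readings are tempting, and the documents do not support them.

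- A reader might infer from section {11b} that participants who become ill are dropped. That section concerns someone who "wishes to discontinue the consumption of experimental products due to poor physical condition experienced during the intervention period". Stopping the product is not leaving the trial; such a person is excluded only if the endpoint data are also missing. Nor does the document show that stopping relates to arm: the trial is double-blind and expects no serious adverse effects from either product.
- A reader might take 0.15 SD and 9% as the size of the problem. Those figures come from an unadjusted completer comparison. The plan promises covariate adjustment, and with the baseline value as a covariate the bias in that scenario disappears.
- A reader might conclude that the comparison is already biased. Every non-zero figure above rests on dropout being unequal, or unequally informative, between arms, and the document gives no such information.

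The imputation sentence can also be read as covering only item-level gaps among attendees. That reading is coherent, but the text does not state it.

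Finally, imputation is no cure by itself. With two time points, imputing endpoints from baseline alone gave almost the same answer as baseline-adjusted completers in simulation (0.152 versus 0.148 SD bias when dropout depended on the outcome; 0.00 for both when it depended on baseline). Imputing a whole missing transcriptome, metabolome or community profile is not routine. This limits the remedy to scalar outcomes and makes the auxiliary data and the delta check the parts that matter.

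**Conclusion.** The point holds in this form and should be fixed. The primary set is complete-case, at best modified ITT, and omits about 16 to 19 of 96 randomised participants under the plan's own allowance. The effect-size rationale does not support the exclusion, the scope of imputation is unresolved, and nothing planned shows how far dropout could move the results.

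The consequence is a risk whose size depends on unstated dropout patterns. It is nil when dropout is similar and equally informative in both arms, and about nil under baseline-dependent dropout if the baseline value is a covariate. It is about 0.10 SD with type I error near 7% in the assumed case of 20% dropout and a 0.5 SD gap in one arm only. The last figure assumes no true effect, unit SD and an unadjusted two-sided 5% test.

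**What to change.** - Call the present set complete-case or modified ITT, and delete the effect-size reason for excluding dropouts.
- For the scalar outcomes (cognitive tests, questionnaires, BMI, alpha diversity), analyse all randomised participants by allocated arm. Use the multiple imputation already named, with baseline values, intake reports and daily health checks as auxiliary variables, or a likelihood model. State the missing-data assumption.
- Adjust for the baseline value of each such outcome, and say so in {20a}.
- Add a delta-adjusted check in which imputed endpoints are made progressively worse, by arm.
- Keep the completer analysis as a sensitivity analysis for these outcomes. For the transcriptome, metabolome and beta-diversity outcomes, keep it as a plainly labelled complete-case analysis.
- Say which missing values the imputation sentence covers.
- Include dropouts' observed records in the daily-health comparison.

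The cost is wording and a little more analysis work, with no new data. The downside is reliance on a stated missing-at-random assumption, which the delta check probes but cannot verify. The change should be made before unblinding.

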### Outcomes {12}

Previous studies have suggested that brown rice has various effects on human health, and we will present evidence concerning these effects and the underlying mechanisms by using a brown rice-derived supplement in this study. Therefore, the overall condition of the immune system, metabolism, constipation, sleep, cognitive function, mental health, and gut microbiota community composition will be co-primary outcomes for comprehensively examining various health aspects. Blood samples will be collected to analyze immune function and metabolism via transcriptome and metabolome analysis, respectively, and stool samples will be collected to evaluate diversity in the gut microbiota.

In addition, we will collect information on the factors that may influence the relationships between consumption of the brown rice-derived supplement and primary outcomes. Various lifestyles could influence the relationships between the consumption of the brown rice-derived supplement and broad health conditions. In particular, daily eating habits and physical activity may strongly impact these relationships. Therefore, we use the brief-type self-administered diet history questionnaire (BDHQ) and a simple questionnaire to evaluate total and domain-specific physical activity [31, 32]. In addition, we will collect data on the overall intelligence quotient (IQ) to control for the influence of IQ on the performance of cognitive tests [33].

Since this study aims to determine the effects of brown rice-derived supplement consumption on various health aspects, all sample collection and measurements, except for daily health, will be performed at two time points (baseline and endpoint), and we will compare the changes in these variables between and within groups. Daily health during the intervention period will be compared between groups. We assume that these variables will change in a positive direction if the brown rice-derived supplement is effective at improving human health.

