### Adverse event reporting and harms {22}

Participants will be asked to actively report any adverse events that occur during the intervention period. The severity of any adverse events, irrespective of their relationship to the study intervention, will be documented in a case report form and assessed using the National Cancer Institute Common Terminology Criteria for Adverse Events v4.0.

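### The exclusion of dropouts without endpoint data is worded for the whole study and, read as written, discards daily symptom records that need no endpoint visit

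*Protocol article*

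**What the plan says.** Section {20c} of the protocol article first describes the set for the primary analysis: "The primary analysis will be based on the intention-to-treat (ITT) principle, but we will include only the randomized participants who participate in data collection". Data from baseline and endpoint are both needed, "irrespective of their degree of adherence to experimental food consumption". A separate sentence, which opens by referring to the study as a whole, then widens the scope: "we will exclude randomized participants who drop out of the study and do not provide endpoint data". The reason given is that the trial studies a nutritional supplement in healthy adults and "we do not expect as great an effect as when medication is administered to a patient group". The section names one further set, a per-protocol set of participants with adherence above 80%, as a sensitivity analysis. Section {20b} says that no additional analyses are planned.

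The Outcomes section {12} sets daily health apart from the measurements taken at baseline and endpoint, and adds: "Daily health during the intervention period will be compared between groups". Under {18a}, the daily health checks cover body temperature and eight symptoms, which include respiratory complaints, stomachache, diarrhoea, loss of appetite and fatigue.

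Section {11b} covers stopping the product. If a participant asks to stop "due to poor physical condition experienced during the intervention period, the intervention will be stopped for that individual". An allergic reaction also ends the intervention for that person. Reasons for stopping are requested. Section {22} deals with adverse events: "The severity of any adverse events, irrespective of their relationship to the study intervention, will be documented in a case report form".

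**The concern.** A rule that requires endpoint data suits outcomes measured as a change from baseline to endpoint. Daily health is not such an outcome. A person who leaves after several weeks has several weeks of usable symptom records, and the rule as worded throws them away. The reason given concerns the size of the expected effect, which is no reason to discard symptoms already observed.

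The loss matters if leaving is related to what is being measured. The protocol itself names poor physical condition and allergic reaction as reasons for stopping the product. Some of those who stop may also leave the study. The daily-health comparison would then be made among people selected partly on their symptoms, and randomisation would no longer protect it. Imputation under {20c} does not repair this, because excluded people are not in the set whose missing values are filled in.

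**Working it through.** **Step 1. Does the rule reach daily health?** Set the sections side by side.
- {20c}, first sentence: a set with data at both time points, tied to the primary analysis.
- {20c}, exclusion sentence: worded for the study, with no outcome named.
- {20c}, per-protocol set: narrower, not wider.
- {12}: daily health is compared between groups and stands outside the two-time-point scheme; no set of its own is given.

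On the plain wording, no stated set includes dropouts. The reach to daily health is the natural reading, not an express statement.

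**Step 2. Who is removed?** Only people who leave and give no endpoint data. {11b} ends the intervention, not participation; {20c} keeps people whatever their adherence and asks everyone to attend the endpoint; {18b} adds an incentive for complete endpoint data.

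**Step 3. How many?** Inputs from Sample size {14}: 40 per group, 96 recruited, 20% dropout.
- The stated figure is reproduced by 80 × 1.20 = 96.
- If exactly 80 complete: 96 − 80 = 16 removed.
- If 20% of 96 drop out: 0.20 × 96 = 19.2, leaving 76.8.

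So about 16 to 19 people could be removed at the planned allowance. How many would leave because of symptoms is not stated.

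**Step 4. What can this do to the comparison?** The protocol gives no symptom rates, so every count here is an assumption. Take n = 48 per arm (96 ÷ 2), h participants with symptoms, and a fraction f of those who leave without endpoint data, with no other dropout. The risk in the retained set is h(1 − f) ÷ (n − hf).

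| Assumed symptomatic (supplement v placebo) | All randomised | f = 0.5, retained set | f = 1 |
|---|---|---|---|
| 4 v 1 | 3/48 = 6.25 points | 2/46 − 0.5/47.5 = 3.3 points | 0 |
| 6 v 2 | 4/48 = 8.3 points | 3/45 − 1/47 = 4.5 points | 0 |
| 8 v 2 | 6/48 = 12.5 points | 4/44 − 1/47 = 7.0 points | 0 |

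Leaving may also differ by arm. With 14/48 v 6/48 symptomatic, the difference is 29.2% − 12.5% = 16.7 points. If 6 and 1 of them leave, it becomes 8/42 − 5/47 = 19.0% − 10.6% = 8.4 points.

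**Step 5. Is the direction fixed?** No. Swap the arms in any row and the same shrinkage hides an excess on placebo. With equal risk, 6/48 in each arm, suppose half of the symptomatic participants leave from the supplement arm only: 3/45 − 6/48 = 6.7% − 12.5% = −5.8 points, an apparent benefit where there is none. If they leave from the placebo arm only, the sign reverses. If leaving is unrelated to symptoms, no bias is expected, only a loss of precision.

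**The case against.** The strongest reply is that the exclusion sentence only explains the primary-analysis sentence before it. Its reason is about efficacy, daily health is not listed among the co-primary outcomes, and a rule keyed to endpoint data fits poorly with an outcome that has no endpoint measurement. This stands in part: the protocol never says that the rule governs daily health. But the sentence carries no limit. If it is confined to the primary analysis, the wording needs to say so.

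A reader might infer more than the documents support:
- **That everyone who stops for a reaction or poor physical condition is lost.** They are not; those who attend the endpoint stay in.
- **That harmed participants disappear from an adverse event comparison.** Section {22} documents all events, and no between-arm comparison is described from which anyone could be removed. The choice of an adverse event set is detail commonly left to the analysis plan or full protocol, so its absence is no finding.
- **That the supplement will look safer than it is.** That requires the supplement to cause symptoms that drive people out, and the protocol has no data on this. It says that serious adverse effects are not expected, and it frames daily health as an outcome hoped to improve, with respiratory symptoms listed beside gut complaints.

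It is also fair to say that the size shown above rests wholly on assumed counts.

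**Conclusion.** The point holds in a limited form. The exclusion is worded for the whole study, its reason does not apply to daily symptoms, and followed as written it discards observed records from people who leave without endpoint data. At the planned allowance that is up to about 16 to 19 of 96 people, for all reasons together. Any bias depends on how far leaving is related to symptoms and on whether this differs by arm; neither direction nor amount can be fixed from the protocol. In the assumed examples, about half of a true difference is lost when half of the symptomatic participants leave, and all of it when all leave. This is a cheap improvement to a stated rule, not a fault that undermines the trial.

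**What to change.** In {20c}, limit the endpoint-data exclusion to outcomes measured at baseline and endpoint. Add that daily-check symptoms are compared by allocated arm in all randomised participants with any daily record, using each person's records up to last contact, as symptom-days over days observed. State that any adverse event summary is likewise not subject to the endpoint-data exclusion.

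The cost is one or two sentences. It uses daily sheets and case report forms already collected, and changes no clinical rule. The downside is unequal observation time. The days-observed denominator allows for shorter follow-up, but it cannot recover symptoms that occur after a person has left.

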### Trial design {8}

This study will be a longitudinal, double-blind, randomized, placebo-controlled prospective intervention trial with a parallel group of healthy adults (see Fig. 1 for an overview of the planned trial design). We designed this study to explore the effects of brown rice-derived supplementation on various health outcomes, including the immune system, cognitive function, gut microbiota, constipation, sleep, and HRQOL. Participants will be randomly assigned to the brown rice-derived supplement group or the placebo group at a ratio of 1:1. This protocol is in accordance with the Standard Protocol Items: Recommendations for Interventional Trials checklist [30]. This study protocol was approved by the Ethics Committee of Tohoku University Graduate School of Medicine (IRB# 2022–1–845) and preregistered in a clinical trial registry (UMIN-CTR ID: UMIN000049330). The committee has peer-reviewed the progress of the study, independent of our research team.

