## Statistical methods

### Statistical methods for primary and secondary outcomes {20a}

The co-primary outcomes will be analyzed to determine whether the consumption of the brown rice-derived supplement is superior to the use of a placebo in terms of positive health effects. The data derived from transcriptome and metabolome analysis will be compared between intervention groups after relevant covariates are controlled for. Microbiome and overall community composition will be compared between intervention groups on the basis of alpha and beta diversity with relevant covariates controlled for. For cognitive function, all outcomes will be compared through an analysis of covariance, with the intervention group set as a between-group factor, the data collection time points as a within-group factor, and the covariates as relevant covariates. The BMI and questionnaire data will be compared through an analysis of covariance controlling for relevant covariates. For continuous variables, the distribution of the data and the fulfillment of the model assumptions will first be assessed. Parametric methods will be used when the relevant assumptions are met; otherwise, appropriate nonparametric methods will be applied.

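### The protocol accepts single regression imputation as an alternative to multiple imputation; for missing endpoint outcomes this understates the standard error, or attenuates the effect if arm is left out of the imputation model

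*Protocol article*

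**What the plan says.** The protocol article's section on non-adherence and missing data (item 20c) ends its missing-data plan with one sentence: "we will address any missing data using multiple imputation or regression imputation". The two methods stand side by side. No variance correction accompanies the second, and it is not confined to any type of variable.

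The same section limits what there is to impute. In the primary analysis "we will include only the randomized participants who participate in data collection at both the baseline and the study endpoint", and "we will exclude randomized participants who drop out of the study and do not provide endpoint data". Imputation therefore concerns values missing among people who attended both time points.

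The target is 40 per group. On recruitment the Sample size section (item 14) says: "We will recruit 96 participants to allow for a potential 20% dropout rate". For part of the outcomes the analysis model is given in the Statistical methods section (item 20a): "The BMI and questionnaire data will be compared through an analysis of covariance controlling for relevant covariates".

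**The concern.** Single regression imputation replaces a missing value by one prediction and then counts it as a measurement. Neither the uncertainty of the fitted coefficients nor, in the deterministic form, the residual scatter reaches the analysis. The residual variance comes out too small and the sample size too large. Multiple imputation exists to repair this, so the two methods are not interchangeable.

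Missing outcomes among attenders are plausible here because the outcomes come from separate sources: stool collected at home, RNA from blood cells, plasma metabolites, computerised tests and several questionnaires. A participant can attend both visits and still have one outcome wholly missing. At stake is the false-positive rate of the superiority comparisons on the co-primary outcomes or, with a different imputation model, the size of the estimated effect.

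**Working it through.** The protocol gives no figure for missing data, so there is none to reproduce. The check asks how large the error would be.

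**Inputs.** From the protocol: 40 per group, 1:1 allocation, analysis of covariance. Assumed, because the protocol states none of them: two-sided alpha of 0.05, correlation of 0.5 between baseline and endpoint, no true effect, and endpoint values missing completely at random in a fraction *m* of 2%, 5%, 10% or 20%.

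**Approximation, arm and baseline in the imputation model.** Imputed values lie on the fitted line and have zero residual. The point estimate equals the complete-case estimate, but two things change:
- The residual sum of squares is unchanged while its divisor grows from about *N*(1 − *m*) to *N*, so the residual variance shrinks by a factor (1 − *m*).
- The design counts *N* participants rather than *N*(1 − *m*), which gives a second factor (1 − *m*).

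Reported SE / correct SE ≈ √[(1 − *m*)(1 − *m*)] = 1 − *m*, so the true alpha ≈ 2[1 − Φ(1.96(1 − *m*))]:
- *m* = 0.02: 1.96 × 0.98 = 1.921, alpha 5.5%
- *m* = 0.05: 1.96 × 0.95 = 1.862, alpha 6.3%
- *m* = 0.10: 1.96 × 0.90 = 1.764, alpha 7.8%
- *m* = 0.20: 1.96 × 0.80 = 1.568, alpha 11.7%

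**Simulation of type I error, 80 participants.** Run A has 4,000 replicates per setting and run B 6,000.

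| Method | 2% missing | 5% | 10% | 20% |
|---|---|---|---|---|
| Single regression, arm in model (A) | 5.2% | 5.7% | 8.5% | 11.1% |
| Single regression, arm in model (B) | 5.6% | 6.7% | 7.8% | 12.1% |
| Single regression plus random residual, arm in model (A) | 5.2% | 6.0% | 8.1% | 9.9% |
| Single regression, arm omitted (B) | 5.1% | 5.2% | 4.8% | 5.0% |
| Multiple imputation, 20 imputations, Rubin's rules (A) | 4.6% | 4.6% | 5.3% | 4.6% |

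In run A the ratio of reported to true SE for deterministic imputation is 0.97, 0.96, 0.88 and 0.80; for multiple imputation it is 0.98 to 1.02. A further run at 80 participants gave about 6%, 7% and 12% at 5%, 10% and 20% missing.

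The 8.5% at 10% missing is probably a little high. Its Monte Carlo standard error is √(0.085 × 0.915 / 4,000) = 0.44 percentage points, and complete-case analysis of the same replicates rejected in 5.4%. Taken together, the results at 10% missing support about 7–8%.

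**Arm omitted.** Imputed values then carry almost no group difference. With a true difference δ and equal missingness by arm, the expected estimate is about (1 − *m*)δ + *m* × 0 = (1 − *m*)δ. It is too small by about 5% at 5% missing and 10% at 10% missing.

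**Where nothing is lost.** In run B, a missing baseline value imputed from another baseline variable gave 4.9%, 5.2%, 4.8% and 5.3% across the four fractions. Isolated items of an 8-item scale imputed from the other items gave 4.8%, 5.2%, 5.1% and 5.3%. Neither shows inflation.

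**The case against.** The strongest reply is that exposure is small. Dropouts are removed, not imputed. The Data management section (item 19) describes digital cognitive testing, staff trained to avoid missing data and double-checked data entry. What remains may be mostly skipped items, missing covariates and an occasional failed sample. At 2% missing the inflation is negligible, and no missingness rate is stated, so 10% is an assumption. All of this stands and limits the size of the point.

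A reader might infer that the 20% dropout allowance sets the missing fraction, giving a type I error of about 12%. The plan as written does not support that, because participants without endpoint data are excluded. A reader might also infer that the error exceeds 5% wherever regression imputation is used. It does not when arm is omitted from the imputation model, or for the baseline values and isolated items tested above. The protocol does not give the imputation model, nor say whether a random residual is added; adding one does not cure the problem at 10% missing.

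The reply that this is detail for the analysis plan holds in part. The number of imputations, the imputation variables and the rule for choosing a method may properly sit there. That the choice would be made after seeing the data is an inference from silence and is not claimed here. What does not fall away is that the protocol itself accepts a single-imputation method.

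**Conclusion.** The point holds in limited form. The protocol accepts a method that, for endpoint outcomes missing among attenders, either understates the standard error (arm in the imputation model) or shrinks the treatment effect (arm omitted). Nothing else in the document corrects this.

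With arm in the model, the type I error is about 5–6% at 2% missing, 6–7% at 5% and 7–8% at 10%. These figures rest on 80 analysed, correlation 0.5, values missing completely at random and analysis of covariance of a single outcome. They do not carry over directly to the transcriptome-wide or beta-diversity analyses, where the mechanism is the same but its size was not computed. The consequence is modest unless an outcome is missing in something like 10% of attenders. It is still worth correcting, since the correction is nearly free.

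**What to change.** Delete the regression-imputation alternative from item 20c, and state for missing outcome values:

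> Missing outcome values will be handled by multiple imputation, with treatment arm and the baseline value in the imputation model, and estimates will be combined by Rubin's rules.

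A likelihood-based model that uses the available outcome values without imputing them would serve equally well. For isolated missing questionnaire items, the instrument's own scoring rule can be applied first.

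The change is a sentence in the protocol, with no new data or participants. Relative to deterministic single imputation with arm in the model, intervals widen by about 1/(1 − *m*): 1/0.98 = 1.02 at 2% missing, 1/0.95 = 1.05 at 5% and 1/0.90 = 1.11 at 10%. That width is the precision the data actually support.
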